# Effects of power training in older patients with multiple sclerosis on neurodegeneration, neuromuscular function, and physical function. A study protocol for the “power training in older multiple sclerosis patients (PoTOMS) randomized control trial

**DOI:** 10.1016/j.conctc.2024.101279

**Published:** 2024-02-19

**Keywords:** Multiple sclerosis, resistance exercise, aging, neuroprotection

## Abstract

**Introduction:**

Approximately one-third of all persons with multiple sclerosis (pwMS) are older, i.e., having an age ≥60 years. Whilst ageing and MS separately elicit deteriorating effects on brain morphology, neuromuscular function, and physical function, the combination of ageing and MS may pose a particular challenge. To counteract such detrimental changes, power training (i.e., a type of resistance exercise focusing on moderate-to-high loading at maximal intended movement velocity) presents itself as a viable and highly effective solution. Power training is known to positively impact physical function, neuromuscular function, as well as brain morphology. Existing evidence is promising but limited to young and middle-aged pwMS, with the effects of power training remaining to be elucidated in older pwMS.

**Methods:**

The presented ‘Power Training in Older MS patients (PoTOMS)’ trial is a national, multi-center, parallel-group, randomized controlled trial. The trial compares 24 weeks of usual care(n = 30) to 24 weeks of usual care and power training (n = 30). The primary outcome is whole brain atrophy rate. The secondary outcomes include changes in brain micro and macro structures, neuromuscular function, physical function, cognitive function, bone health, and patient-reported outcomes.

**Ethics and dissemination:**

The presented study is approved by The Regional Ethics Committee (reference number 1-10-72-222-20) and registered at the Danish Data Protection Agency (reference number 2016-051-000001). All study findings will be published in scientific peer-reviewed journals and presented at relevant scientific conferences independent of the results. The www.clinicaltrials.gov identifier is NCT04762342.

## Introduction

1

Multiple sclerosis (MS) is characterized by focal lesions and whole brain atrophy caused by an autoimmune dysfunction [1]. Such neurodegeneration, quantifiable by MRI [2], results in a plethora of symptoms including motor, cognitive, and sensory impairments [1], affecting the lives of people with MS (pwMS) [3]. Importantly, the prevalence of older (≥60 years of age) pwMS has increased substantially and will expectedly continue to do so in the coming decades [[4], [5], [6], [7]]. Today, approximately 1/3 of all pwMS are older [[7], [8], [9]]. This introduces a combined challenge comprised of ageing and MS, which separately have deteriorating effects on whole brain volume [[10], [11], [12], [13], [14]], regional brain volume [[12], [13], [14], [15], [16]], physical function [[17], [18], [19], [20]], neuromuscular function [[21], [22], [23], [24]], and bone health [25,26].

Although sparsely investigated, the combined effect of MS and ageing is known to impair walking capacity [[27], [28], [29], [30], [31]], lower limb neuromuscular function [30] including muscle power [29], and increase frailty [32,33] in older pwMS when compared to age-matched healthy controls (HC). This limited physical function is paralleled by the reduced self-reported walking ability of older pwMS [27,34,35]. Unfortunately, there is a paucity of research related to potential interventions counteracting the combined deleterious consequences of ageing and MS, making further research into this MS subgroup highly warranted.

Progressive resistance exercise (PRE) has resulted in improved physical and neuromuscular function in young and middle-aged pwMS [36,37], with dynamic muscle strength as well as rate of force development (RFD) being particularly susceptible towards adaptation [21]. Of note, such adaptations are predominantly attributed to functional adaptations of the CNS, with improved neural drive [[38], [39], [40]]. In addition, data from a pilot randomized controlled crossover study involving n = 35 pwMS suggests that 24 weeks of PRE improves cortical thickness and reported a trend towards reduced whole brain atrophy [41]. Despite these positive effects of PRE in pwMS, it has not yet been investigated in older pwMS; however, data from older healthy individuals show that PRE induces positive effects on both physical function [42,43] and neuromuscular function [42,44]. This is mainly achieved through increased neural drive to the muscles [42,45] as well as muscle hypertrophy [46,47]. The former is suggestive of an improved CNS ability to recruit and fire motor neurons following PRE.

PRE can be performed as progressive power training (PPT; PRE performed with moderate-to-high loading at maximal concentric movement velocity) hereby increasing demands of the CNS to activate the muscle. PPT induces comparable improvements in muscle strength as traditional PRE, but greater improvements in muscle power [48,49]. This is important, as pwMS have substantial muscle strength reductions during fast concentric contractions [21] and since muscle power, more so than muscle force, is a strong predictor of physical function in older adults [50,51]; nevertheless, power training has only been sparsely investigated in pwMS so far [52], and still not in older pwMS where it may have the most profound effects.

Consequently, the primary aim of the present study is to compare the effects of 24 weeks of power training to a “usual care” control group on neurodegeneration (i.e., annualized whole brain atrophy rate) in older pwMS (≥60 years). A secondary aim is to evaluate the effects of 24 weeks power training on additional macro and micro brain structures, neuromuscular function, physical function, cognitive function, bone health and patient-reported outcomes.

For the primary aim, we test the hypothesis that older pwMS performing 24 weeks of power training will elicit a reduced annualized whole brain atrophy rate compared with the control group. For the secondary aim we test the hypothesis that performing 24 weeks of power training will improve brain micro and macro structures, neuromuscular, physical, cognitive function, bone health, and patient-reported outcomes.

## Methods

2

### Study design

2.1

The PoTOMS trial is a 24-week national, multi-center, parallel group, randomized controlled trial (RCT) with 24-weeks of follow-up. The present study compares an intervention group of older pwMS receiving 24 weeks of high-load progressive power training (PPT) to a control group of older pwMS receiving usual care, comprising standard healthcare provided to pwMS within the Danish healthcare system. The study design of the PoTOMS trial is depicted in Fig. 1. This study protocol conforms to the SPIRIT statement, and the trial is registered at www.clinicaltrials.gov (registration number NCT04762342).

**Fig. 1 fig1:**
[figure not shown]
Study design of the PoTOMS trial.

### Recruitment and eligibility

2.2

PwMS will be recruited via four Danish regional MS clinics (Aarhus University Hospital, Esbjerg Hospital, Odense University Hospital, and Rigshospitalet), events hosted by the Danish MS Society, www.forsøgsperson.dk, and social media. All pwMS will be supplied with a leaflet explaining the study (design and content) and an invitation to participate. Interested pwMS will then receive detailed written study information and a leaflet from the national ethical committee explaining the rights of participants in health science research projects according to Danish legislation. The project coordinator will screen potential participants according to the following inclusion and exclusion criteria. Older pwMS will be eligible for inclusion if they are:-≥ 60 years of age.-clinically diagnosed with MS according to the McDonald criteria [53].-having an EDSS ≤6.5.-capable of self-transportation to testing at Aarhus University and Aarhus University Hospital.-capable of self-transportation to training, if randomized to the PPT group.

PwMS will be excluded if they are:-having comorbidities (cardiovascular, respiratory, orthopedic, or other neurological diseases than MS) affecting PPT participation or testing.-having a pacemaker.-having metallic implant(s) that prevents MRI scans.-having untreated osteoporosis; t-score below −2.5 and a history of low energy fracture or t-score below −3.0.-participating in ≥2 sessions per week of structured PRE and have done so for the past 3 months.-having cognitive impairments that prevent the participant from understanding training and testing instructions.

All participants will provide informed consent to the trial leader (TG) before participation.

### Sample size

2.3

The present study is powered based on the primary outcome; percentage total brain volume change after 24 weeks of PRE in pwMS quantified by structural image evaluation, using normalization, of atrophy (SIENA) [41] and the assumption that PPT is ∼15% more effective than traditional of PRE [49,54]. A two-sample two-sided power calculation showed that a total of 30 subjects are needed in each group to adequately power the study (α = 0.05; power = 0.8; control mean = 0.3204 (SD 0.5253); exercise mean = −0.0148 (SD 0.2698); dropout rate = 16%).

### Random allocation procedure

2.4

Randomisation to either the PPT group or the control group will be performed after baseline testing by the project coordinator in a 1:1 allocation ratio. Allocation is done by the sealed envelope principle.

### Intervention

2.5

#### High-load progressive power training

2.5.1

PwMS randomized to the PPT group will receive 24 weeks of supervised PPT with two weekly sessions and usual care. To improve adherence to PPT, four sites delivering exercise will be established in the cities where the recruiting MS centres are located (Aarhus, Copenhagen, Esbjerg, and Odense). The PPT intervention will be delivered at university fitness facilities and supervised by exercise physiology students who, besides their educational background, will be thoroughly educated and instructed in how to deliver the specific PPT program. All trainers will receive a detailed booklet describing the training program and related procedures; further, a ‘hotline’ to the lead researcher exists if any questions should arise. Education and instruction of the trainers include correct performance of exercises and safety measures regarding training older pwMS [55,56]. Training sessions will throughout the intervention period, be offered 5 days a week. The intention is to carry out all sessions in small groups without surpassing a 4:1 ratio of participants to the supervising trainer. Individual sessions will nevertheless be carried out if required.

An overview of the PPT intervention can be seen in Table 1. The first four weeks of the PPT program serve as an introduction, focusing on the correct execution of exercises. Weeks 5–8 emphasise the performance of exercises with the correct muscle contraction velocity, which is essential for PPT, and this exercise manipulation is used in the remaining weeks. During weeks 9–24 additional, translational power exercises also involving power training aspects are added to the program (referred to as ‘translational mesocycle blocks’). This small part of the PPT program is aimed at facilitating the translation of exercise adaptions to daily physical function. The translational mesocycle blocks consist of exercises that include walking accelerations, fast chair raises, and balancing exercises. There is also some upper body PPT added. The translational mesocycle is separated into 4 blocks lasting 4 weeks each. Blocks 1 and 3 and 2 and 4, respectively, share the same exercises, except that the relative intensity and volume are progressed from block 1 to 3 and from block 2 to 4. Altogether The PPT program targets the whole body, yet with a primary focus on the lower extremities.

**Table 1 tbl1:**
[figure not shown]
Overview of the PPT intervention.

Introduction to resistance exercise (light grey marking), introduction to PPT (grey marking), PPT (dark grey marking), and extension mesocycle (crossed lines). The extension mesocycle blocks adds exercises such as intermittent walking to the intervention. Abbreviations: PPT: High-load progressive power training.

*Warm-up:* Each session begins with a warm-up, consisting of ergometer cycling for 2 min at low intensity directly followed by 2 min at moderate intensity. Subsequently, standing balance is performed in 2 sets of 15 s for each leg. The balance exercises are gradually progressed by reducing the level of support when possible (e.g., advancing from supporting with two hands to one hand). To finalize the warm-up, participants perform 2 × 30 s alternating knee raises where the anterior thigh reaches horizontal. When participants can perform ≥26 repetitions, ankle weights are added with 1 kg increments for each leg.

*PPT:* After the warm-up, the PPT follows (see description in Table 2), which consists of five exercises performed in machines (bilateral leg-press, bilateral plantar flexion performed in leg-press machine), unilateral knee extension, bilateral lying leg curl) and one exercise performed with an elastic band (unilateral banded dorsal flexion). All exercises, both bilateral and unilateral, are performed with the intent to match the relative intensity in both limbs. The PPT program is planned so that the exercises are performed in three mesocycles: First as 3 sets of 12 repetitions at 14-RM during weeks 1–8; second as 3 sets of 10 repetitions at 12-RM during weeks 9–16; and third as 3 sets of 8 repetitions at 10-RM during weeks 17–24. Progression of external load is performed when a participant can perform ≥2 repetitions more than planned according to participants own rate of perceived exertion (RPE) scale, ranging from 0 to 10 (10 being maximal exertion) [57]. Unilateral banded dorsal flexion is based on band tension as external resistance and hence load is solely determined by RPE. Here participants are expected to reach an RPE of 7-to-9.5.

**Table 2 tbl2:** Detailed description of the PPT intervention.

Load (RM)	14 (week 1–8), 12 (week 9–16), 10 (week 17–24)	
Repetitions (number)	12 (week 1–8), 10 (week 9–16), 8 (week 17–24)	
Sets (number)	3	
Rest between sets (min)	1½	
Session duration (min)	60	
Duration of training period (weeks)	24	
Time between sessions (hours)	≥48	
Exercise manipulation	Traditional PRE (week 1–4), PPT (week 5–24)	
Velocity of PTT	The concentric contraction is performed as fast as possible, and the eccentric contraction duration is 1–2s	
Exercise	Loading	Performed in week
Bilateral leg-press	Weight stack machine	1–24
Bilateral plantar flexion	Weight stack machine	1–24
Bilateral knee extension	Weight stack machine	1–24
Unilateral banded dorsal flexion	Elastic band	1–24
Bilateral lying leg curl	Weight stack machine	1–24
Back extension	Weight vest	1–24
Shoulder press	Dumbbell	9-12, 17-20
Seated row	Weight stack machine	9-12, 17-20
Chest press	Weight stack machine	13-16, 21-24
Lat pull-down	Weight stack machine	13-16, 21-24

Abbreviations: PPT: High-load progressive power training. RM: Repetition maximum, PRE: Progressive resistance exercise.

Evaluation of progression in training exercises is done by a 5 R M test performed in bilateral leg-press and unilateral knee extension in week 1 (session 2), week 5 (session 9), week 9 (session 17), week 13 (session 25), week 17 (session 33), and week 21 (session 41).

*Translational extension mesocycle:* The exercises added in the four blocks of ‘translational extension mesocycle’ are walking drills, dumbbell shoulder press, seated row, chair rise, countermovement jump, chest press, lat. pull-down, and interval walking. These exercises are added to facilitate the translation of PPT effects to daily activities and to secure variation of the training to facilitate adherence.

Documentation of PPT is performed by registering the number of performed training sessions, repetitions, sets, external load, and RPE. Session adherence to PPT is evaluated as number of sessions attended, expressed as a percentage of the total number of planned sessions [58]. Content adherence to the intervention is measured as number of repetitions performed in the PPT expressed as a percentage of the total number of planned repetitions. Per protocol completion of the exercise intervention is defined as 40 or more of the 48 planned sessions and an exercise session is considered completed with an ≥80% content adherence.

#### Control group

2.5.2

To evaluate effects of the PPT intervention in older pwMS, we will compare it with a group of older pwMS receiving usual care only, thus serving as the control group. Usual care encompasses the health care services offered for pwMS within the Danish health care system. The specific health care offered depends on various factors, including disability status, and disease severity, but could include services as disease-modifying treatments, symptom management, various aids (ranging from walking aids to caretakers), and rehabilitation. The control group will not receive any additional intervention but are allowed to continue their usual activities (or start new activities if desired).

### Outcomes

2.6

All outcomes will be assessed at week 0, 24, and 48. An overview of outcomes can be seen in Table 3.

**Table 3 tbl3:** Overview of test.

	Pre intervention test	Post intervention test	Follow-up test
Brain MRI			
MP2RAGE	x	x	x
T2 Space, dark fluid	x	x	x
DKI	x	x	x
Leg MRI			
Leg 2D Dixon	x	x	x
Muscle strength			
Bilateral leg press	x	x	x
Hand grip	x	x	x
Knee extension	x	x	x
Knee flexion	x	x	x
Plantar ankle flexion	x	x	x
Dorsal ankle flexion	x	x	x
Neural function			
ITT	x	x	x
EMG	x	x	x
Cognition			
SRT	x	x	x
SDMT	x	x	x
Clinical disability			
EDSS	x		
Physical function			
T25FWT	x	x	x
SSST	x	x	x
6MWT	x	x	x
9SSA	x	x	x
NHPT	x	x	x
1STS	x	x	x
5STS	x	x	x
Standing balance	x	x	x
Blood sample			
Neurodegenerative factors	x	x	x
Neurotrophic factors	x	x	x
Immunological factors	x	x	x
Bone metabolism	x	x	x
Body composition			
DXA	x	x	x
Physical activity			
Accelerometry	x	x	x
Questionnaires			
MSIS	x	x	x
MSWS	x	x	x
HADS	x	x	x
MFIS	x	x	x
EQ5D	x	x	x
FES-I	x	x	x
PSQI	x	x	x
ADL	x	x	x
BPI	x	x	x

Abbreviations: MP2RAGE: Magnetization Prepared 2 Rapid Acquisition Gradient Echo, DKI: Diffusion kurtosis imaging, T25FWT: Timed 25-foot walk test, SSST: Six spot step test, 6MWT: Six-minute walk test, 9SSA: Nine step stair accent, NHPT: Nine-hole peg test, 1STS: one time sit-to-stand test, 5STS: five time sit-to-stand test, SRT: Selective reminding test, SDMT: Symbol digit modality test, EDSS: Expanded disability status scale, DXA: Dual-energy X-ray absorptiometry MSIS: Multiple sclerosis impact scale, MSWS: Multiple sclerosis walking scale, MFIS: Modified fatigue impact scale, HADS: Hospital anxiety and depression scale, EQ-5D: Euro quality of life 5-dimension, FES-I: Falls efficacy scale-international, PSQI: Pittsburgh sleep quality index, ADL: Activities of daily living, BPI: Brief pain inventory.

#### Primary outcome

2.6.1

The primary outcome of the study is MRI-derived whole brain atrophy rate measured using SIENA [59]. All MRI scans will be performed on the same 3-T MRI scanner (MAGNETOM Skyra, Siemens Medical Systems, Erlangen, Germany) at baseline, 24 weeks (post-intervention), and 48 weeks (follow-up). MRI analyses will be performed by a blinded assessor. Annualized whole brain atrophy rate is quantified using structural T1-weighted 3D Magnetization Prepared 2 Rapid Acquisition Gradient Echo images [60] acquired with a Field-of-view (FOV) of 256 × 256 mm^2^, matrix of 256 × 256, spatial resolution of 1 × 1 × 1 mm^3^. Repetition time (TR) is 5000 ms, Echo time (TE) is 2.98 ms and Inversion time (TI) is 707 ms/2500 ms. The image processing will follow the steps outlined by Riemenschneider et al. [61].

#### Secondary outcomes

2.6.2

Analysis of macrostructural changes of brain tissue based on T1 weighted images consists of percentage change in brain parenchymal fraction, white matter volume, grey matter volume, and cortical thickness using FACE [62]. Whole brain white matter lesion load and lesion count are derived from fluid attenuated inversion recovery (FLAIR) images using LST [63]. The FLAIR sequence is a 3D SPACE sequence with FOV = 250 × 364 mm^2^, matrix = 220 × 320, and spatial resolution = 1.1 × 1.1 × 1.2 mm^3^. TR/TE/TI = 5000/386/1800 ms.

To study brain microstructure a diffusion kurtosis imaging (DKI) sequence is applied. From this, a range of parameters describing the tissue microstructure can be derived. These include fractional anisotropy, mean diffusivity, axial diffusivity, radial diffusivity, axonal signal fraction, intra-axonal diffusivity, extra-axonal axial diffusivity, and extra-axonal radial diffusivity. Finally, the DKI sequence is utilized to measure white matter fibre orientations by calculating tractography maps. These are important for understanding the association between functional symptoms and structural connections affected by white matter lesions. DKI is based on single-shot diffusion weighted EPI sequence with b-values of 250, 1000 and 2000 s/mm^2^ and 84 diffusion directions in total. FOV is 216 × 216 mm^2^, matrix is 128 × 128, and spatial resolution is 1.7 × 1.7 mm^2^ with a slice thickness of 3 mm. TR/TE is 9300/97 ms.

The PPT intervention is expected to affect brain regions involved in motor function [[64], [65], [66], [67], [68], [69], [70]]. Thus, a separate analysis for these regions is conducted. The following nuclei are segmented and processed to study changes in macro- and microstructure: thalamus, hippocampus, putamen, caudate, globus pallidus, corticospinal tract, cingulate gyrus, corpus callosum, cervical spinal volume, and motor cortex.

A multi-slice 2D, T1-weighted spin echo DIXON sequence is acquired bilaterally for the leg and thigh. Thirty slices with a thickness of 3 mm will be acquired on the thigh and the calf separately. FOV is 450 × 309 mm^2^, matrix is 640 × 352, and spatial resolution is 0.70 × 0.88 mm^2^. TR/TE is 1260/11 ms. Using ITK snap (version 3.8.0 or higher) regions of interest are drawn using the high resolution and contrast DIXON sequence. The region of interest includes the rectus femoris, vastus medialis, vastus lateralis, vastus intermedius, gastrocnemius, soleus, and tibialis anterior. From these segmentations, analysis of muscle cross-sectional area is performed in ITK snap.

##### Physical functional

2.6.2.1

The timed 25-foot walk test (T25FWT), is a validated measure of maximal walking speed in pwMS [71]. It is performed on a clearly marked 25-foot course and participants are instructed to walk 25 feet as walk twice at their usual walking speed and twice as fast (although safe) as possible [71]. The result is the average time of the two walking tasks. A change exceeding 20% is considered a clinically meaningful change for the T25FWT [72].

The 6-minute walk test (6MWT) is a measure of walking endurance in pwMS [73,74]. The test is performed in a 30 m hallway [73] in accordance with the ATS statement script [75] and participants are instructed to walk as fast (although safe) as possible. A clinically meaningful change in distance walked in the 6MWT is 21.6 m or more in pwMS [74]. Additionally, the 6MWT also determines motor fatigability in pwMS following the procedures previously described by Leone et al. [76].

The six-sport step test (SSST) measures complex walking [77] and requires changes in direction, balance, and coordination. The SSST have sufficient construct validity and discriminative properties [78], test–retest agreement, and reliability [79]. The test is performed in accordance with the original script of Nieuwenhius et al. [77] applying the adjustments proposed by Callesen et al. [79]. The test is conducted on a 1 × 5 m rectangular course where the patient walked as fast (although safe) as possible while pushing five wooden blocks out of circles marked on the floor. The test is performed two times with each foot, and the score is the average time of the four tries [77].

The 9-step stair accent (9SSA) test reflects an important task of daily living. The test is performed using an indoor standard flight of stairs (depth of 29 cm and height of 17 cm). Participants are instructed to ascend the 9 steps one step at a time as fast (although safe) as possible [30]. The use of railing and/or their assistive device is allowed if needed. Two trials of stair climbing are performed, using the best trial as the result.

The 5-times sit-to-stand (5STS) and 1-time sit-to-stand (1STS) measures chair rise capacity [80] and functional lower extremity muscle power [29]. Participants are instructed to rise from a seated position and sit back down five times as fast as possible, yet safely. Then, participants are instructed to perform one maximal chair rise. Both chair rise tests are performed according to the script of Møller et al. [80]. A linear encoder (CRONOJUMP, Bosco system, v1.8.1, Spain; sampling rate 1000 Hz) is fastened to a belt placed on the hip of the participant and provides displacement of the approximated centre of mass of the participant during the 1STS. The latter follows the procedure described by Stagsted et al. [29]. The participants complete two trials and the best serve as the final test result and results are reported for 5STS as time to completion and average power and peak power for 1STS.

The nine-hole peg test (9HPT) measures manual dexterity and upper extremity function. It is conducted with the 9HPT testing device consisting of a container, nine pegs, and nine holes in a symmetrical square pattern. The participants are instructed to insert the nine pegs one by one into each of the nine holes and then remove them again individually, as fast as possible. The test is performed twice with both the dominant and non-dominant hand. The average time of all four trials is used as the outcome [81]. A clinically meaningful change in the 9HPT is an improvement of 20% or more [82].

Standing balance is measured in accordance with the script of the short physical performance battery [83]. Here participants are asked to balance with their feet together side-by-side for 10 s and if successful advance to standing in semi-tandem, in tandem, and using only the weakest leg. If the participants fail to keep 10 s of balance in one stance the test will not proceed to subsequent stands.

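### The T25FWT is presented as maximal walking speed, but its scoring sentence, read literally, averages usual-pace and fast-pace walks into one score

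*Protocol article*

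**What the plan says.** Four statements in the T25FWT paragraph of section 2.6.2.1 (Physical functional) of the protocol article bear on the point:

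- Construct: the test "is a validated measure of maximal walking speed in pwMS".
- Procedure: participants "walk twice at their usual walking speed and twice as fast (although safe) as possible", which makes four walks under two instructions.
- Score: "The result is the average time of the two walking tasks".
- Interpretation: "A change exceeding 20% is considered a clinically meaningful change for the T25FWT".

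Table 3 has one row for the T25FWT at each of the three visits and does not divide it by pace. The abstract places physical function among the secondary outcomes, and section 2.8 (Statistics) analyses those with the same mixed model as the primary outcome.

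**The concern.** The two tasks named just before the scoring sentence are the usual-pace walk and the fast-pace walk. If the score is the average over both, it contains usual-pace time and is no longer a measure of maximal walking speed. Because the usual-pace walk normally takes longer, it also carries at least half the weight in an average of times.

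This matters for this intervention in particular. Section 2.5.1 and Table 2 describe training built on moving as quickly as possible in the concentric phase, and the introduction motivates it by the strength deficit of people with MS in fast contractions. Fast walking is therefore a natural place to look for an effect. A pooled score would understate a gain confined to that condition, and a reader who sets the reported change beside the 20% figure would be comparing it with a different quantity from the one the paragraph describes.

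If the sentence means something else, the article does not say which average carries the maximal-speed label, and the choice stays open when the data are scored.

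**Working it through.** **Reading the text.** Three readings of the scoring sentence are possible:

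1. The average over the usual-pace and fast-pace tasks, giving one pooled score.
2. The average of the two walks within each pace, giving two scores.
3. The average of the two fast walks only.

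Reading 1 is the literal one: the sentence speaks of tasks, two tasks have just been named, and one result is announced. It conflicts with the maximal-speed description. Readings 2 and 3 remove the conflict but have to be supplied by the reader.

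The wording used for other tests points both ways. For the six spot step test, "The test is performed two times with each foot, and the score is the average time of the four tries"; for the nine-hole peg test, "The average time of all four trials is used as the outcome". Repetitions are called tries or trials there, which suggests that tasks means conditions here (reading 1). But where four attempts are averaged the article says four, which suggests that two here means two walks (readings 2 or 3).

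**Size of the dilution under reading 1.** The article gives no T25FWT figure to reproduce, and no walking times. Inputs:

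- g: proportional fall in fast-pace time. I use 20%, the article's own meaningful-change figure.
- r: usual-pace time divided by fast-pace time. Assumed, range 1.0 to 1.8.
- k: proportional usual-pace gain as a share of the fast-pace gain. Assumed, range 0 to 1.

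Set baseline fast time to 1 and usual time to r. The baseline pooled mean is (1 + r)/2. After the change, the fast time has fallen by g and the usual time by k·g·r, so:

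proportional pooled change = g(1 + k·r)/(1 + r)

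share of the fast-pace change retained = (1 + k·r)/(1 + r)

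The share is below 1 whenever k is below 1.

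| k | r = 1.0 | r = 1.35 | r = 1.8 |
|---|---|---|---|
| 0 | 50% | 43% | 36% |
| 0.25 | 62.5% | 57% | 52% |
| 0.5 | 75% | 71% | 68% |
| 0.75 | 87.5% | 86% | 84% |
| 1 | 100% | 100% | 100% |

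Worked cases for a 20% fall in fast time:

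- r = 1.35, k = 0: 0.20 × 1/2.35 = 8.5% in the pooled score.
- r = 1.35, k = 0.5: 0.20 × 1.675/2.35 = 14.3%.
- k = 1, any r: 20%.

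In reverse, a 20% pooled change requires a fast-time fall of 0.20(1 + r)/(1 + k·r). That is 40% to 56% at k = 0, 26.7% to 29.5% at k = 0.5, and 20% at k = 1. Scored on the fast walks alone, a 20% fall registers as 20% throughout.

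**The case against.** The strongest reply is that the paragraph is badly edited rather than wrongly designed. The instruction sentence is visibly garbled, so the next sentence should not be held to its letter, and a within-pace average fits the maximal-speed label better. That stands in part: pooling cannot be asserted as the trial's definition. It does not remove the point, because the literal reading contradicts the construct and no other section corrects it.

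A reader might infer that real gains in fast walking are roughly halved. The article does not support that as a general statement. It holds only if usual pace hardly changes, and nothing says it will not. Section 2.5.1 adds walking accelerations, walking drills and interval walking, and aims for carry-over to daily function. Over the assumed range, the loss runs from none to about 64%.

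A reader might also infer that a 20% responder criterion becomes nearly unreachable. No such criterion is used: section 2.8 plans a mixed-model comparison, and the 20% is background on clinical meaning, like the figures given for several other outcomes. Whether that figure was derived for fast walking alone depends on a cited source that is not at hand. Nor does dilution of the mean change by itself show a loss of power. That depends on the SDs at each pace and the correlation between them, which are not given.

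Finally, a condensed article may leave trial-level scoring to the full protocol. Here, however, it states a scoring rule, and the rule as stated does not fit the construct.

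**Conclusion.** The point holds in limited form. The stated T25FWT score, read literally, mixes usual and fast pace and conflicts with the maximal-speed description in the same paragraph. A within-pace reading is possible, and the article does not settle which is meant.

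If the paces are pooled, the score keeps 50% to 36% of a fast-pace change when usual pace is unchanged, 75% to 68% when usual pace gains half as much proportionally, and 100% when both gain equally. These figures rest on an assumed usual-to-fast time ratio of 1.0 to 1.8. Comparison of the result with the 20% figure is distorted to the same degree, as a matter of interpretation and not of a planned test.

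This is one secondary outcome. The primary analysis of brain atrophy and the sample size in section 2.3 are unaffected.

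**What to change.** Replace the scoring sentence with one that defines the T25FWT score as the mean of the two fast walks, and attach the maximal-speed label and the 20% interpretation to that score. Report the mean of the two usual-pace walks as a separate, named outcome.

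The cost is one sentence and one extra line in the outcome list. All four walks are already performed, so no further testing is needed; rescoring requires only that the time of each walk was kept. The definition should be fixed before T25FWT results are examined by group.
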